### Data analysis plan

The main null hypothesis to be tested is that there is no difference between the three groups in hours in competitive employment or education in the 18-month follow-up period. All randomized participants will be analyzed, including those who stop receiving treatment, according to the intention-to-treat principle. All continuous outcome measures, including the primary outcome “hours in competitive employment or education”, will be analyzed by using generalized linear models. In situations in which the continuous measure is non-normally distributed, a non-parametric model will be used. Multiple imputations will be used to impute a distribution of missing values. Furthermore, linear mixed models with repeated measurements and unstructured covariance matrixes will be used to assess the potential interaction between time and intervention. The dichotomous secondary outcome “work or education at some point during the follow-up period” will be analyzed by using logistic regression. The secondary outcome “time-to-employment or education” will be analyzed by using the Cox proportional hazards model. All models will be adjusted for the stratification variables.

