The effects of the IPS intervention have been investigated in a number of randomized clinical trials, and reviews of these trials suggest that IPS is superior to other types of vocational rehabilitation programs in regard to obtaining competitive employment [6–9]. A review including 15 high-fidelity IPS trials shows an average employment rate among the IPS participants of 58.9 % compared with 23.2 % for control participants [7]. All of the control groups consisted of either treatment as usual, typically referral to the state vocational system, or well-established alternative vocational models [7]. Outcomes related to wages earned and hours worked were also found to be superior among those receiving the IPS intervention [7]. Previous research has not found that IPS leads to increased stress, exacerbation of symptoms, or other harmful clinical outcomes [8, 10]. The results of a recent Cochrane systematic review investigating IPS-supported employment for adults with severe mental illness additionally suggest that, compared with other vocational approaches, IPS is effective in improving a number of vocational outcomes relevant to people with severe mental illness [11]. However, the authors conclude that evidence from the included randomized trials was of “very low quality” mainly due to a high risk of bias (i.e., not describing allocation concealment). Furthermore, the meta-analysis excluded a majority of previous trials because of skewed data and populations of fewer than 200 people [11].

Moreover, it has been suggested that long-term job retention and economic self-sufficiency could be further improved by adding cognitive remediation and work-related social skills training to the intervention [10, 11]. Impairment in these functions is frequent among persons receiving IPS services and is known to be related to employment outcomes in persons with severe mental illness [12–14]. Two small-scale trials have found improved effects when the intervention was enhanced with either cognitive remediation or work-related social skills training [13, 15–17].

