### Randomization

After the assessment, a central web-based randomization will be performed by the Copenhagen Trial Unit [23] according to a computer-generated allocation sequence with permuted blocks of varying sizes. The allocation sequence and varying block sizes will be concealed from the investigators. A research secretary will perform the allocation by logging on to a website by using a personal password. Previous research has shown an effect of sex and of work history on vocational outcomes [24, 25]. Therefore, the allocation sequence will be stratified by sex and by work history (more or less than 2 months of competitive employment during the last 5 years). Furthermore, participants will be stratified by work readiness by using match categories, a tool used in Danish job centers [26]. We will assess the likelihood that the participant is ready to apply for competitive employment and will be self-sufficient within 3 months (match 2 or 3). Finally, the participants will be stratified by site.

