	Obtained through interview	Cognitive function measured with the Brief Assessment of Cognition in Schizophrenia [32] (BACS)	X	X
	Obtained through interview	Function measured with Personal and Social Performance (PSP) Scale [31]	X	X
	Self-reported questionnaire	Self-efficacy measured with General Self-Efficacy (GSE) scale [37]	X	X
	Self-reported questionnaire	Self-esteem measured with the Rosenberg Self-Esteem scale [38]	X	X

To avoid the risk of multiplicity and type I errors, we will limit our secondary outcomes to outcomes with at least 80 % power. Other outcomes are considered “exploratory” when drawing conclusions. This means that we will consider any statistically significant result in any of these outcomes as exploratory or hypothesis-generating. This is because we have no sample size estimation for these outcomes, and thus the risk of an early false positive is increased; it is further increased because of the risk of multiplicity as a result of too many outcomes.

Exploratory outcomes cover the 30 and 60 months of register follow-up along with additional vocational measures that will provide a more nuanced picture of vocational status, including average monthly earnings and hours of work per week among those who obtain competitive employment. Furthermore, a range of non-vocational outcomes such as client satisfaction, health-related quality of life, empowerment, recovery, and substance abuse will be used to address other important factors hypothesized to influence the participants. Psychopathology will be measured to ensure no adverse effects of the intervention.

All exploratory and safety measures and the assessment instruments used are outlined in Tables 3 and 4. Trained and certified research assistants will perform all assessments. Inter-rater reliability tests will be performed prior to the trial and at least quarterly throughout the assessment period on the following instruments: Scale for the Assessment of Negative Symptoms [35], Scale for the Assessment of Positive Symptoms [35], PSP scale [31], and Hamilton Depression Scale (HAM-D6) [36]. The aim is to achieve an interclass correlation coefficient of more than 0.7. Consensus ratings will be performed on the remaining instruments.

**Table 3 Tab3:** Explorative measures and data collection

Outcomes	Source of collection	Assessment	Baseline	18-month follow-up	30 + 60-month register follow-up

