### Sample size and power calculation

No previous IPS trials or similar studies have been conducted in Denmark that could contribute to an estimation of the expected average number of hours of work among participants in the IPS intervention. A European IPS multicenter trial found a difference between the IPS group and the control group (vocational services) of 150 h in competitive employment in an 18-month follow-up period, and standard deviation was 500 [19]. A difference of 150 h in competitive employment or education is considered clinically relevant. If the outcome within each intervention group is normally distributed with a standard deviation on 500 and with a true mean difference of 150 between the intervention and the control group, the present trial will need 250 participants in both intervention arms and additionally 250 control participants to be able to reject the null hypothesis that the population means of the experimental and control groups are equal with probability (power) of 80 %. The type I error probability associated with the null hypothesis is 1.25 %. A type I error of 1.25 % was chosen to give the possibility to make four comparisons: (1) IPS versus service as usual, (2) IPS versus IPS enhanced, (3) IPS enhanced versus service as usual, and (4) IPS + IPS enhanced versus service as usual. If we encounter difficulties in recruiting 250 participants to each group, we will exclude comparison (4) as a primary comparison. With three primary comparisons, we use a type I error of 1.67 % in the sample size calculation, accumulating a sample size of 236 patients in each group. Power calculations on calculations of the secondary outcome measures were carried out (Table 5) and indicate that a sample size of 250 patients per group would be adequate to detect relevant significant differences.

**Table 5 Tab5:** Power calculation

Outcome measure	δ expected difference in mean	σ expected standard deviation	α	Power	Reference
Days to first employment or beginning of education	68	45	0.0125	1.000 (*t* test)	Bond et al. [8] (2008),
Cognitive function	0.3	0.7	0.0125	0.989 (*t* test)	McGurk et al. [13] (2005)
The Brief Assessment of Cognition in Schizophrenia [32]					
Function measured with Personal and Social Performance (PSP) scale [31]	7	14	0.0125	0.999 (*t* test)	Kawata et al. [31] (2008). Nasrallah et al. [46] (2008) (No IPS studies use PSP scale. δ is estimated)

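### The primary hours model could gain some precision, probably a modest amount, if baseline BACS were prespecified as a covariate beside the stratification variables

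*Protocol article*

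**What the plan says.** - **Adjustment set.** The Data analysis plan ends with "All models will be adjusted for the stratification variables". It names no further covariate for hours, for any work or education, or for time to work or education.
- **Stratifiers.** Under Randomization, "the allocation sequence will be stratified by sex and by work history"; work readiness (match category) and site are added. Sex and work history are justified there by earlier evidence that they affect vocational outcomes. None of the four measures cognition.
- **Cognition as a predictor.** The Background discusses impairment in cognitive and work-related social functions and says it "is known to be related to employment outcomes in persons with severe mental illness". It gives no correlation.
- **Availability.** In Table 2 (Outcome and assessments), the entry that begins "Cognitive function measured with the Brief Assessment of Cognition in Schizophrenia [32] (BACS" is marked for baseline and for 18 months. Randomization takes place after the assessment, so the baseline score precedes allocation.
- **Sizing.** Under Sample size and power calculation, "A difference of 150 h in competitive employment or education is considered clinically relevant", and the outcome is taken as "normally distributed with a standard deviation on 500". "The type I error probability associated with the null hypothesis is 1.25" per cent, and 250 per arm is given for 80% power.
- **Model for hours.** A generalized linear model, replaced by a non-parametric one if the measure is not normally distributed.

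**The concern.** The protocol picks two of its stratifiers because they predict vocational outcomes. By the same standard cognition qualifies, on the protocol's own statement, and it is to be collected at baseline. Yet it is not in the named adjustment set for the primary outcome.

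In a linear model, adjusting for a pre-randomization predictor leaves the treatment contrast unbiased and reduces its standard error by removing the variance that the predictor explains. It also removes from the realized estimate the part of any chance baseline difference that runs through that predictor. At stake is precision on the primary comparisons, at a sample size whose nominal power is close to 80%. The validity of the test is not in question.

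**Working it through.** **Inputs from the protocol article.** Difference δ = 150 h; SD σ = 500 h, with no reduction for covariates; n = 250 per arm; α = 0.0125 per comparison; power 80%. The fallback is 236 per arm at α = 1.67%. Sidedness is not stated.

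**Input not in the document.** ρ, the correlation of baseline BACS with hours that remains after the stratifiers. It is an assumption, taken over 0.1 to 0.4.

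**Step 1: reproduce the plan's figure.** By the normal approximation,

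n = 2(z₁₋α/₂ + z₀.₈)² (σ/δ)² = 2(2.498 + 0.842)² (500/150)² ≈ 248 per arm,

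against the stated 250. A one-sided test would need 212, so the plan is two-sided. With 250 per arm the standard error is 500 × √(2/250) = 44.7 h and the noncentrality is 150/44.7 = 3.354. Power is 80.1% from the noncentral t distribution (80.4% by normal approximation). The fallback gives 233 against the stated 236, with power 80.4%. The plan's sizing reproduces.

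**Step 2: add baseline BACS.** The residual SD becomes 500 × √(1 − ρ²). The equivalent sample size is 250/(1 − ρ²) per arm. Power is from the noncentral t with n = 250 and α = 0.0125.

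| Assumed ρ | Variance removed | Residual SD (h) | SE (h) | Power | Gain (points) | Equivalent n per arm |
|---|---|---|---|---|---|---|
| 0 | 0% | 500.0 | 44.7 | 80.1% | – | 250 |
| 0.1 | 1% | 497.5 | 44.5 | 80.6% | 0.5 | 253 |
| 0.2 | 4% | 489.9 | 43.8 | 82.0% | 1.9 | 260 |
| 0.3 | 9% | 477.0 | 42.7 | 84.3% | 4.2 | 275 |
| 0.4 | 16% | 458.3 | 41.0 | 87.5% | 7.4 | 298 |

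In the fallback design, ρ = 0.3 takes power from 80.4% to 84.4%.

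**Step 3: allow for the stratifiers.** Step 2 applies ρ to the raw SD of 500 h, but the planned model already adjusts for the stratifiers. Suppose they explain a share R² of the variance (also an assumption). The residual SD is then 500 × √[(1 − R²)(1 − ρ²)].

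- R² = 5%: power before BACS is 82.5%.
- R² = 10%: power before BACS is 84.8%. Adding ρ = 0.3 gives a residual SD of 500 × √(0.90 × 0.91) = 452.5 h and power 88.4%. The gain is about 3.7 points before rounding, against 4.2 in Step 2.

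The true power of the planned analysis is therefore likely to sit a little above the nominal figure, and the extra gain from BACS a little below the table.

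**The case against.** The strongest reply is that nothing here is wrong. Adjusting for the stratification variables after stratified randomization is sound, those variables were themselves chosen partly as predictors, and the planned test reaches its stated power without BACS. The text does not say that only these variables will be used, and an unseen analysis plan may add others. Work history and work readiness may overlap with cognition, so ρ may be small. **All of this stands**, and it makes the point an efficiency suggestion.

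The figures also assume a linear model. The plan switches to a non-parametric model for non-normal data and does not say how covariates would enter it. This stands too, so the fix has to cover that case.

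A reader might infer more than the document supports:

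- **That the primary comparison has no reserve at all.** The 80.1% ignores whatever variance the planned stratifier adjustment removes.
- **That the gain is large.** Five points needs ρ of about 0.33, or 11% of the variance left after the stratifiers. Nothing in the document supports that value or a higher one such as 0.5.
- **That imbalance in cognition matters most for IPS versus enhanced IPS.** Chance imbalance in a predictor can affect every pairwise contrast alike and is already covered by the type I error. That the enhanced arm trains cognition bears on effect modification.
- **That the logistic and Cox models gain in the same way.** The linear result does not carry over. There the effect becomes conditional on the added covariate, and no gain has been computed.
- **That PSP has equal support.** The Background speaks of cognition and work-related social skills and does not name PSP.
- **That BACS will be complete.** Table 2 gives a schedule, with no data on completeness.

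**Conclusion.** The point holds as a modest efficiency improvement. The protocol schedules a pre-randomization measure of something that it describes as related to employment, and it fixes an adjustment set for the hours model that does not name it. The direction of the benefit is clear under a linear model; its size cannot be derived from the document. For ρ of 0.1 to 0.3 the gain is about 0.5 to 4 percentage points of power, equivalent to about 3 to 25 participants per arm, and somewhat less in power terms if the stratifiers already reduce the SD. At ρ = 0.4 it would be about 7 points.

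This rests on the plan's own δ, σ, n and α, a two-sided test, a linear model for hours, and an assumed ρ. It does not show that the planned analysis is invalid or underpowered.

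**What to change.** Before unblinding, amend the Data analysis plan so that the primary hours model adjusts for the stratification variables and, in addition, the baseline BACS composite as a continuous covariate, with missing baseline values imputed without using treatment arm. State that if the non-parametric fallback is used, the covariate is carried into a covariate-adjusted rank method or another robust method. Keep the stratifier-only model as a sensitivity analysis, and leave the sample size unchanged.

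Adding baseline PSP, or extending the adjustment to the logistic and Cox models, is optional. If either of those two models is extended, say that its effect is then conditional on the added covariate.

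The cost is one sentence, one covariate from data already scheduled, and simple imputation of any missing baseline scores. No new data or participants are needed. The article reports 480 participants randomized as of January 2015 out of a planned 750, and the analysis is to be done on coded groups, so the change could still be prespecified at that stage.

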### Outcome and assessments

The primary outcome is “hours in competitive employment or education” measured from baseline to 18-month follow-up. Employment and enrollment in education will be identified by using register data. Hours in competitive employment will be extracted from an extended version of the Danish Register for Evaluation of Marginalization (DREAM) database administered by the National Labor Market Authority [30]. The DREAM database contains information on employment, sickness leave, and education eligible for state education grants, disability pension, social security, and sickness benefits. The register covers the entire population, and data can be linked to a range of different registers, including the Danish income register, making it possible to obtain the exact number of employment hours. Data on education will be extracted from education statistics hosted by Statistics Denmark (http://www.statbank.dk) and supplemented by data from interviews for more detailed information on part-time studies.

The primary outcome will be supported by several other secondary and explorative outcome measures. Secondary outcomes are work or education at some point during the follow-up period (yes/no), days to first employment or beginning of education, cognitive impairment, functional level, self-esteem, and self-efficacy assessed at baseline and 18-month follow-up. Data on employment and education will similarly be extracted from registers. Furthermore, semi-structured interviews using the Personal and Social Performance (PSP) scale [31] and the Brief Assessment of Cognition in Schizophrenia [32] will be used to assess cognitive impairment and functioning. Standardized validated survey instruments, including the Rosenberg self-esteem scale [33] and the General Self-Efficacy scale [34], will be used to assess self-esteem and self-efficacy. All secondary outcomes and the assessment instruments used are outlined in Table 2.

**Table 2 Tab2:** Primary and secondary outcomes and data collection

Outcomes	Source of collection	Assessment	Baseline	18-month follow-up
Primary outcome	Register-based/Interview	Hours in competitive employment or education in follow-up period		X
Secondary outcomes	Register-based	Competitive employment or education at some point during follow-up period		X
	Register-based	Days to first employment or beginning of education		X

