Self-efficacy measured with General Self-Efficacy scale [37]	0.28	0.85	0.0125	0.880 (*t* test)	Tsang et al. [14] (2010)
Self-esteem measured with the Rosenberg Self-Esteem scale [38]	0.3	0.55	0.0125	0.992 (*t* test)	Mueser et al. [47] (2004), Howard et al. [18] (2010), Drake et al. [48] (1999). None of the studies shows difference in mean. σ is between 0.55 and 0.68.
Competitive employment or education during follow-up period	50 % vs. 34 %	-	0.0125	0.807 (chi-squared test)	Bond et al. [8] (2008)
Dichotomous yes/no					

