## Discussion

This is the first trial investigating the effects of IPS in Denmark and will be one of the largest randomized trials investigating IPS to date. As a comparison, 14 trials included in a Cochrane review showed a median sample size per arm of 70 participants and a range of between 20 and 156 [11]. Furthermore, this trial will be the first large-scale trial, with a long follow-up period, enhancing the IPS intervention with both cognitive remediation and social skills training. The design of the trial has several strengths. Firstly, a sample size calculation was made according to the primary outcome, hours in competitive employment or education. The power is estimated for all secondary outcome measures, showing that a sample size of 750 participants is sufficient to show a relevant effect size with a power above 80 %. Secondly, the risk of selection bias related to allocation sequence generation and concealment is limited, as the Copenhagen Trial Unit performs a central web-based randomization according to a computer-generated allocation sequence. Thirdly, assessors are blinded, and blinding will be used wherever possible to prevent bias. Data will be analyzed according to the intention-to-treat principle, which together with an intense follow-up of patients should limit the risk of attrition bias. Finally, internal validity is addressed by implementing fidelity ratings. The fidelity ratings have high priority and will be conducted throughout the trial period to ensure that evidence-based practice is adhered to.

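### Free improvement: name the baseline score as a covariate for the four scale-based secondary outcomes (BACS, PSP, General Self-Efficacy, Rosenberg)

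*Protocol article*

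**What the plan says.** The Outcome and assessments section lists "cognitive impairment, functional level, self-esteem, and self-efficacy assessed at baseline and 18-month follow-up" among the secondary outcomes, and Table 2 confirms both time points for BACS, PSP, General Self-Efficacy and Rosenberg. The same section sets a rule for admitting secondary outcomes: "we will limit our secondary outcomes to outcomes with at least 80 % power".

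Under Data analysis plan, continuous outcomes "will be analyzed by using generalized linear models", missing values are multiply imputed, and "linear mixed models with repeated measurements and unstructured covariance matrixes will be used to assess the potential interaction between time and intervention". The section closes with one covariate rule: "All models will be adjusted for the stratification variables". The Randomization section gives these variables as sex, work history, work readiness (match category) and site.

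Table 5 gives self-efficacy a power of 0.880 by t test, from a difference of 0.28, an SD of 0.85 and alpha 0.0125. No attrition rate or baseline correlation is given anywhere.

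**The concern.** A person's earlier score on a scale usually predicts the later score on the same scale. Where that holds, leaving the baseline score out of the model makes standard errors larger than they need to be. The article states an adjustment set, and for these four outcomes it does not mention the most obvious covariate, which is already being collected.

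The mixed model does not clearly fill the gap. It is introduced as an addition, it is aimed at an interaction, and it is not ranked against the generalized linear model. Two analyses of one secondary outcome, using baseline differently, could give different answers.

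What is at stake is precision on secondary outcomes. The primary outcome, hours in employment or education, has no baseline measurement in Table 2 and is not affected.

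**Working it through.** **Inputs from the article (Table 5 and Sample size section).** Self-efficacy: difference 0.28, SD 0.85, alpha 0.0125, 250 per arm. Sidedness is not stated; two-sided reproduces the printed power. **Assumed, not in the article:** baseline-to-18-month correlation r of 0.3, 0.5 or 0.7, equal variances at both times, and loss of 0 to 30 %.

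**1. The plan's own figure.** Standard error = 0.85 × √(2/250) = 0.0760. Noncentrality = 0.28 / 0.0760 = 3.68. Exact noncentral-t power = 0.8797. This matches the stated 0.880, so the printed value is an unadjusted t-test power on the raw SD with every participant measured.

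**2. Variance of the three contrasts, relative to the unadjusted comparison.**
- Unadjusted 18-month comparison: 1
- Difference in change (time-by-intervention interaction, two time points, baseline means left free by arm): 2(1 − r)
- Baseline-adjusted comparison (ANCOVA): 1 − r²

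Since 2(1 − r) − (1 − r²) = (1 − r)², the change contrast never beats ANCOVA for r < 1. It beats the unadjusted comparison only when 2(1 − r) < 1, that is r > 0.5.

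**3. Self-efficacy power at 250 per arm, no loss (exact t).**

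| Assumed r | Unadjusted | Change contrast | Baseline-adjusted |
|---|---|---|---|
| 0.3 | 0.880 | 0.727 | 0.912 |
| 0.5 | 0.880 | 0.880 | 0.959 |
| 0.7 | 0.880 | 0.988 | 0.996 |

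At r = 0.5 the variance is multiplied by 0.75, equivalent to 1/0.75 = 1.33 times as many participants. At r = 0.7 the factor is 0.51.

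**4. Does self-efficacy keep 80 % power without adjustment?** With no loss, yes (0.880). With n = 250 × (1 − loss) and complete cases:

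| Assumed loss | n per arm | Unadjusted power |
|---|---|---|
| 10 % | 225 | 0.837 |
| 15 % | 212.5 | 0.812 |
| 20 % | 200 | 0.783 |
| 25 % | 187.5 | 0.751 |
| 30 % | 175 | 0.716 |

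The crossing lies between 208 per arm (0.802) and 207 per arm (0.7998), a loss of about 17 %. At 20 % loss, baseline adjustment would give 0.827, 0.902 or 0.982 for r = 0.3, 0.5 or 0.7.

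**5. Effect of the planned imputation.** If the imputation model used the baseline score (the article does not list its variables), an unadjusted analysis would recover part of the loss. The variance factor relative to complete data is (1 − r²)/(1 − loss) + r². At 20 % loss and r = 0.5 this is 0.75/0.8 + 0.25 = 1.1875, so effective n = 250/1.1875 = 211 and power is about 0.81. The same steps give about 0.79 at r = 0.3 and 0.83 at r = 0.7.

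**6. The other three scales, unadjusted, complete cases.** At 30 % loss (175 per arm), the same t-test formula gives about 0.93 for BACS (0.3, SD 0.7) and 0.98 for PSP (7, SD 14). Self-esteem (0.3) gives about 0.95 at SD 0.68, the upper end of the range in Table 5, and more at SD 0.55. None comes near 0.80.

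**The case against.** The strongest reply is that this is a journal article. Full covariate lists, the ranking of models and the imputation variables are commonly left to an analysis plan that is not shown. The covariate sentence does not say that nothing else will be adjusted for, and the repeated-measures model does bring in the baseline scores. Much of this stands: the article does not exclude baseline adjustment, and nothing here is a contradiction. What remains is that the article states an adjustment rule for every model and these scales would be better served by a longer one. The mixed model, as described, targets a contrast that is weaker than ANCOVA. A version that constrains baseline means to be equal across arms would come close to ANCOVA, but the article does not describe one.

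A reader might infer that self-efficacy needs baseline adjustment to satisfy the 80 % rule, or that Table 5 overstates its power. The article does not support either. The 0.880 is already unadjusted and reproduces. The rule is applied at the design stage and is met. A shortfall needs an assumed loss above about 17 %, and the Discussion plans close follow-up of participants. Even at 20 % loss the shortfall is 0.783 against 0.80, and imputation using baseline could remove it at r = 0.5.

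A reader might also infer that an unadjusted analysis is biased by chance baseline imbalance. In a randomized trial it is not. Such imbalance is part of the sampling variation that the standard error already covers, so this is a matter of precision.

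**Conclusion.** The point holds as an efficiency improvement with no real downside. It does not show an error in any stated figure. Naming the baseline score as a covariate would add precision for all four scales at any non-zero correlation. The gain in power matters most for self-efficacy, which has the smallest margin of the four. The size of that gain depends on the correlation, which the article does not give, so the range above should be read as illustrative. The Discussion's statement that Table 5 is "showing that a sample size of 750 participants is sufficient to show a relevant effect size" is not undermined by this point.

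**What to change.** Add one sentence to the Data analysis plan, or confirm that the full analysis plan already contains it: for BACS, PSP, General Self-Efficacy and Rosenberg, the main analysis is the 18-month score regressed on arm, baseline score and the stratification variables. Include the baseline score in the imputation model and label the repeated-measures mixed model a sensitivity analysis. Apply the same rule to the exploratory and safety scales that Tables 3 and 4 show with a baseline, such as GAF, SF-12, the Empowerment Scale, EQ-5D, SAPS, SANS and HAM-D6. Scales collected only at 18 months (recovery and satisfaction) stay as they are.

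The cost is the sentence and one degree of freedom per model. The baseline data are already scheduled, and the sample size and Table 5 need no change. The wording should be fixed before the analysts see outcome data by group.
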